8 During the concomitant medication review, both the dosage and frequency of use will be investigated.

9 For the herbal medicine strategy group, adverse events will be confirmed via weekly phone calls starting from week 1 after herbal medicine administration. For TKM treatment group, these assessments were conducted at weeks 1–2, 2–1, 3–1, 4–1, and 5–1. If not conducted during the first visit of the respective week from week 2 to 5, it may be conducted during the second visit of that week.

10 For treatment compliance verification, in the herbal medicine strategy group, the number of days herbal medicine was not taken since receipt was assessed weekly from weeks 1 to 5. At week 7, the total number of prescribed herbal medicine packs and the number of remaining packs were recorded in the CRF. For TKM treatment group, the total number of administered treatments will be recorded in the CRF at week 7.

11 Participants in the herbal medicine strategy group will visit weeks 0, day 10, and day 20 to receive and take a 10-day supply of herbal medicine, totaling 30 days.

12 The frequency of usual TKM treatment will generally adhere to a standard of twice per week but may be adjusted to 1–3 times per week based on the clinician’s judgment regarding the patient’s symptoms, with the total number of sessions not exceeding 10.

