### Procedures for randomization

2.4

An independent statistician will prepare the randomization list in SAS version 9.1.3 (SAS Institute Inc., Cary, NC, United States), using a fixed seed to ensure reproducibility. At visit 1, eligible participants—those satisfying the inclusion and exclusion criteria—will be assigned to either the herbal medicine or standard traditional Korean medicine (TKM) group through block randomization with a 1:1 ratio. Each participant will receive a site-specific enrollment number and a randomization code delivered via sealed envelopes handled by an external party. During screening, investigators will secure informed consent, document eligibility, and issue consecutive screening codes (e.g., S1-01). Once eligibility and consent are verified, participants will be enrolled and given a unique allocation code (e.g., R1-01) linked to the randomization schedule.

This open-label study maintains assessor blinding: outcome evaluators (research nurses or residents), who neither provide treatment nor know group assignments, will perform assessments in isolated rooms. Items at risk of unblinding—such as credibility/expectancy scales, cost records, medication logs, and adverse event reports—are exempt from this blinding.

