#### Analysis of safety endpoints

2.7.3

Adverse events (AEs), including those leading to withdrawal and serious AEs, will be summarized by treatment group and compared using chi-squared or Fisher’s exact test. Incidence rates of all AEs and herbal medicine-specific AEs will be reported.

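### In weeks 1–5 adverse events are elicited by telephone in the herbal arm but at treatment visits in the control arm, and the planned between-arm test makes no allowance for it

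*Protocol article*

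**What the plan says.** **Herbal arm, weeks 1–5.** Table 1, footnote 9: "adverse events will be confirmed via weekly phone calls starting from week 1 after herbal medicine administration". Under footnote 11 these participants "will visit weeks 0, day 10, and day 20 to receive and take a 10-day supply of herbal medicine, totaling 30 days".

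**Control arm, weeks 1–5.** Footnote 9: "For TKM treatment group, these assessments were conducted at weeks 1–2, 2–1, 3–1, 4–1, and 5–1". It also allows some flexibility within a week: "If not conducted during the first visit of the respective week from week 2 to 5, it may be conducted during the second visit". Footnote 12 sets treatment at a usual two sessions a week, adjustable between one and three, "with the total number of sessions not exceeding 10".

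**From week 7.** Table 1 gives both arms the same AE assessments at weeks 7, 12, 19 and 26, and the same laboratory tests at week 7.

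**Analysis.** Section 2.7.3 says that AEs, including serious AEs and those leading to withdrawal, "will be summarized by treatment group and compared using chi-squared or Fisher’s exact test". It continues: "Incidence rates of all AEs and herbal medicine-specific AEs will be reported". It does not mention how an event was elicited.

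**Blinding.** Section 2.4: "Items at risk of unblinding—such as credibility/expectancy scales, cost records, medication logs, and adverse event reports—are exempt from this blinding".

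**The concern.** Safety is a stated aim of the trial (section 2.1), and the abstract's conclusion promises robust evidence on it. A between-arm comparison of AE incidence is a comparison of safety only if an event of a given kind has the same chance of being recorded in either arm. Here mode of elicitation is fully confounded with arm throughout active treatment, when treatment-related events are most likely. A telephone call depends on recall and self-report. At a session, staff can also see an event for themselves.

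The Discussion acknowledges detection bias from the open-label format and names blinded outcome assessment among its mitigations. Section 2.4 takes AE reports out of that blinding, so this safeguard does not reach the safety data. At stake is whether a reported AE difference, or the lack of one, can be attributed to treatment.

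**Working it through.** **1. What differs and what does not (Table 1 and footnotes 3, 9, 11, 12)**

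| Feature | Herbal arm | Control arm |
|---|---|---|
| Scheduled AE assessments, weeks 1–5 | weekly (5) | weekly (5) |
| Mode in weeks 1–5 | telephone | in person, at a treatment visit |
| In-person contacts after week 0, before week 7 | 2 (day 10, day 20) | up to 10 |
| AE assessments at weeks 7, 12, 19, 26 | common | common |

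Scheduled frequency is matched. Moving a control assessment to the second visit of the week changes the day, not the count. The figure of 10 is a ceiling: footnote 3 lets the control arm's 1–1 visit fall on the same day as week 0, which leaves up to 9 later contacts, and footnote 12 allows fewer.

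**2. How much could detection alone move the result?**

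The plan gives no AE risk and no detection rate, so it has no figure to reproduce. What follows is illustration. The only inputs from the document are 37 per arm (section 2.3), two-sided α = 0.05 (section 2.7) and the two tests (section 2.7.3). True risk and detection probabilities are assumptions.

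Formula: observed incidence = true risk × detection probability, with the same true risk in both arms.

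Assume a true risk of 20%, detection of 90% in person and 60–75% by telephone:

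- Control: 0.20 × 0.90 = 18%, or 0.18 × 37 = 6.7 participants.
- Herbal: 0.20 × 0.60 = 12% (4.4 participants) to 0.20 × 0.75 = 15% (5.6 participants).
- Spurious difference: 3 to 6 percentage points.
- Standard error of the difference, √[(p₁(1−p₁) + p₂(1−p₂))/37]: for 18% against 15%, √[(0.1476 + 0.1275)/37] = 8.6 points; for 18% against 12%, √[(0.1476 + 0.1056)/37] = 8.3 points.

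The probability of a significant difference when true risk is equal comes from exact enumeration of two binomials with n = 37 each (chi-squared without continuity correction):

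| True risk | Detection, herbal / control | Observed | Chi-squared | Fisher |
|---|---|---|---|---|
| 20% | 0.90 / 0.90 | 18% / 18% | 5.1% | 2.6% |
| 20% | 0.75 / 0.90 | 15% / 18% | 6.5% | 3.3% |
| 20% | 0.60 / 0.90 | 12% / 18% | 11.4% | 6.1% |
| 40% | 0.70 / 0.90 | 28% / 36% | 11.4% | 7.5% |
| 60% | 0.70 / 0.90 | 42% / 54% | 17.2% | 11.9% |

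Swapping the two detection probabilities leaves the rejection rates unchanged and reverses the apparent advantage: 0.70 / 0.90 gives a risk ratio of 0.78, and 0.90 / 0.70 gives 1.29. With equal detection of 0.90 the chi-squared rate stays at 4.7–5.1% for true risks of 20–60%.

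**The case against.** Much of the case on the other side stands.

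- **Both arms are asked weekly, and share a schedule from week 7.** Correct. The asymmetry is limited to mode, setting and extra in-person contact in weeks 1–5.
- **Direction is not shown.** Correct. A reader might infer that the plan favours a finding that herbal medicine is safer. The documents do not support that as a fact: they hold no detection rates, and a dedicated safety call could elicit as much as a question put during a treatment session, or more. More in-person observation of control patients makes that direction plausible and no more.
- **Bleeding and fainting seen at sessions are real control-arm harms.** Correct. Section 2.9 lists them as acupuncture-related, so recording them is not in itself bias.
- **The blinding exemption covers both arms.** Correct. It creates no difference between arms. It only means that blinding cannot be offered as the remedy.
- **The effect on the test is small at low AE risk.** Correct for the 20% illustration: the shift is below one standard error. The more likely harm there is a distorted reported incidence rather than a false significant result.
- **A pragmatic design accepts such differences.** This does not answer the point. The Background defends different delivery of treatment. AE elicitation is a research measurement and need not follow the delivery pattern.

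**Conclusion.** The point stands in a limited form. The plan confounds mode of AE elicitation with arm in weeks 1–5 and tests the incidences against each other with no allowance for it, so a detection difference can be read as a safety difference. That much follows from the text alone. Size and direction do not. Under the 20% illustration the bias is 3–6 points, with rejection rates of 6.5–11.4% (chi-squared) or 3.3–6.1% (Fisher). It grows if AEs are commoner or the detection gap is wider.

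A reader might also infer that the damage cannot be repaired once data are collected. That goes too far: if the source of each event were recorded, a sensitivity analysis would be possible. The article describes no such field. The change is worth making because section 2.2 says recruitment is still under way and the remedy is cheap. It does not put the efficacy analysis in question.

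**What to change.** 1. **Amend Table 1, footnote 9** so that both arms receive the same scripted AE questions in the same mode at weeks 1–5, asked by study staff who do not treat the participant. A telephone call is one option. The week-5 call can be combined with the telephone survey in footnote 6, which is not limited to one arm. If a blinded assessor makes that call, the AE questions should follow the NRS and ODI, or be put by someone else.
2. **Add a CRF field** for the source of each event: scripted elicitation, spontaneous report, or observed at a session.
3. **Amend section 2.7.3.** Keep all events in the main safety summary. Add a sensitivity comparison limited to events from the common scripted contacts and the common visits at weeks 7–26. The restricted set should not become the main analysis, because it could drop genuine control-arm harms that were seen at a session and not reported again.
4. **If collection cannot be changed**, present the AE comparison descriptively and state the difference in mode as a limitation.

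Cost: at most 5 × 37 = 185 short calls in the control arm, or 4 × 37 = 148 if the week-5 survey call is used, plus one CRF field. Participants already enrolled will have been followed under the present scheme, so the date of the change should be recorded and reported.

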### Inclusion and exclusion criteria

2.2

Participant recruitment for this clinical trial is currently ongoing based on the following pre-specified eligibility criteria. The First Participant Recruitment Date was August 1, 2025. Participating institutions are engaging in competitive recruitment without specific enrollment targets assigned to each site.

#### Inclusion criteria

2.2.1

Participants will be enrolled if they meet the following criteria:

(1) Male or female adults aged ≥19 years at the time of screening.(2) Presence of disc bulging or worse in the lumbar spine, confirmed by MRI or CT scans, with clinical correlation to radiating pain symptoms.(3) Reporting a Numeric Rating Scale (NRS) score of ≥3 and ≤6 for radiating leg pain over the past week, indicating mild to moderate pain suitable for evaluation of traditional alternative therapies as a primary intervention, while not precluding adjunctive conventional treatments where clinically appropriate.(4) Willingness to participate in the clinical study and provision of written informed consent.

#### Exclusion criteria

2.2.2

Participants will be excluded if they meet any of the following criteria:

(1) Congenital lumbar spine malformations or lumbar spine surgery within the past 3 months.(2) Red flag symptoms suggestive of cauda equina syndrome (e.g., bladder/bowel dysfunction, saddle anesthesia).(3) Lumbar spine co-morbidities, including tumors, fractures, or infections.(4) Direct lumbar injection therapy (e.g., steroids) within the past week.(5) Current treatment for psychiatric disorders (e.g., depression, schizophrenia).(6) Severe medical conditions interfering with treatment or participation (e.g., gastrointestinal, cardiovascular, hypertensive, diabetic, renal, hepatic, or thyroid disorders).(7) Pregnancy, breastfeeding, or plans to become pregnant.(8) Contraindications to acupuncture (e.g., bleeding disorders, severe diabetes with infection risk).(9) Contraindications to herbal medicine, including diseases affecting drug absorption/metabolism, digestive disorders post-surgery, anticoagulant therapy, or severe liver/kidney disease (AST, ALT, *γ*-GTP, or serum creatinine >2x upper normal limit at screening).(10) Participation in another clinical study within 1 month prior to screening or planned participation during the study or within 6 months post-screening.(11) Inability to provide written informed consent.

### Sample size calculation

2.3

The target sample size for this PRCT was rooted on a previous research (17). The required sample size was determined by calculating the minimum number of participants needed to detect a clinically meaningful difference between the intervention and control groups, specifically for the primary outcome measure, using a superiority design. The effect size (Cohen’s d) was estimated at 0.5, representing a moderate difference we aimed to detect. Assuming an alpha level (*α*) of 0.05 (two-sided) and a statistical power (1 − *β*) of 80% (0.80), the required number of participants per group (n) was calculated using the formula for comparing two independent means: *n* = 2 × *δ*2(Zα/2 + Zβ)2 × *σ*2, where Zα/2 and Zβ are the standardized normal deviates corresponding to the significance level and power, σ is the estimated standard deviation, and δ is the minimum clinically important difference. We estimated the standard deviation (σ) to be 10 points and set the minimum detectable difference (δ) to be 5 points on the primary outcome scale. Accounting for an anticipated 15% attrition rate, the total required sample size was adjusted from N_calculated_ to N_final_ to ensure adequate power at the study’s conclusion, resulting in a target enrollment of 74 participants (37 per group). Target sample sizes are listed in Table 2. This trial is powered for a superiority outcome, but a secondary, exploratory non-inferiority (NI) analysis is planned to assess the comparative effectiveness or safety of the intervention if the superiority hypothesis is not met. This approach is clinically relevant for pragmatic trials, evaluating whether the intervention is “not worse” than the control within a predefined NI margin (*Δ*). However, the sample size of 74, calculated for superiority, is likely insufficient for a definitive NI trial, as NI analyses typically require larger samples to ensure the confidence interval of the treatment difference lies within Δ. To address this, the manuscript will clarify that the NI analysis is exploratory and hypothesis-generating, underpowered for this endpoint, and will report the NI margin and two-sided 95% confidence interval for the primary outcome difference.

**Table 2 tab2:** Target sample size of the study.

Category	Control group	Intervention group	Total participants
Efficacy evaluable cases	33	33	66
Total sample size (incl. 10% dropout)	37	37	74

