Nevertheless, limitations persist. Enrolling patients with disc pathology of “bulging or worse” captured real-world TKM presentations of neurocompressive radiculopathy and axial pain yet compromised cohort uniformity, potentially attenuating effect-size precision and complicating interpretation across severity strata. Subgroup analyses stratified by radiological grade will temper this concern and strengthen applicability to routine practice. The open-label format, inevitable in pragmatic research, invited performance and detection biases from treatment awareness; furthermore, the modest sample (*n* = 74), powered for superiority, constrained non-inferiority exploration. Blinded outcome assessment, intention-to-treat, and per-protocol analyses mitigated these risks, though larger trials incorporating placebo arms remain warranted. Finally, absence of fixed treatment algorithms fostered clinical variability, risking dilution of intervention-specific signals and internal validity. Subsequent investigations should enforce protocol standardization, mandate granular documentation of therapeutic rationales, and deploy techniques such as propensity score matching to sharpen causal inference and broaden generalizability.

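### The stated inputs (d = 0.5, two-sided 5%, 80% power) need 63–64 evaluable participants per arm, but Table 2 has 33, which gives about 52% power by the stated method; the attrition rates also conflict

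*Protocol article*

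**What the plan says.** Section 2.3 (Sample size calculation) describes a superiority design and the formula for comparing two independent means. Its inputs are:

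- The effect size "was estimated at 0.5, representing a moderate difference we aimed to detect".
- The significance level, "of 0.05 (two-sided) and a statistical power" "of 80% (0.80), the required number of participants per group (n").
- An SD of 10 points. The authors "set the minimum detectable difference (δ) to be 5 points on the primary outcome scale", which agrees with d = 0.5 (5/10). The same symbol δ is defined there as the minimum clinically important difference.
- Attrition: "Accounting for an anticipated 15% attrition rate".

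The result is given as "resulting in a target enrollment of 74 participants (37 per group"). Table 2 in the same section lists 33 efficacy-evaluable participants per arm (66 in total) and 37 per arm (74 in total) in a row labelled "Total sample size (incl. 10% dropout").

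Section 2.3 says that the trial is powered for superiority. The Discussion repeats this, calling the sample of 74 "powered for superiority, constrained non-inferiority exploration". The primary outcomes (Abstract; sections 2.1 and 2.7.2) are two: change from baseline to week 7 in radiating-pain NRS and in ODI. Section 2.3 refers to a single primary outcome scale and does not say which.

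**The concern.** A two-sample comparison at d = 0.5 with 80% power is a familiar benchmark, and it takes roughly twice the 33 per arm shown in Table 2. The section prints a complete set of inputs and a result that they do not produce. Fuller documents elsewhere could not make both true.

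What is at stake is how a non-significant result is read. A reader told that the trial has 80% power for a 5-point difference would take such a result as fair evidence against a difference of that size. By the stated method, a real 5-point difference would be missed about half the time. A failure to show superiority also opens the non-inferiority analysis. Section 2.3 openly calls that analysis exploratory and underpowered, but makes no similar disclosure for superiority, where the stated power is wrong.

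**Working it through.** **Inputs (section 2.3):** δ = 5, σ = 10, d = 0.5, two-sided α = 0.05, power 80%. Allocation is 1:1 (section 2.4).

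**1. Attempt to reproduce 33 per arm.** The standard formula for two independent means is n per arm = 2 (z₁₋α/₂ + z₁₋β)² σ²/δ². (The printed formula does not show the division by δ². The fraction may have been damaged in text extraction, so nothing here rests on it.)

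- Normal approximation: 2 × (1.960 + 0.842)² / 0.5² = 62.8, so 63 per arm.
- Noncentral t: 63.8, so 64 per arm.

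Table 2 has 33. Variants do not rescue it: a one-sided test needs 50–51 per arm, leaving out the factor 2 gives 31.4 (32), and a one-sample or paired formula gives 33.4 (34). The last two come close to 33 but are not the stated calculation.

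**2. Power at the planned size** (unadjusted two-sample t-test, two-sided 5%, d = 0.5):

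| Evaluable per arm | Power |
|---|---|
| 31 (37 × 0.85 = 31.45) | 49% |
| 33 (Table 2) | 52% |
| 37 (no attrition) | 56% |
| 64 | 80% |

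With 33 per arm, 80% power is reached at d = 0.70, or 7 points at SD 10. With 31 it is reached at d = 0.72.

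**3. Attrition.**

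- 10% (Table 2): 33/0.90 = 36.7, so 37 per arm. This matches.
- 15% (text): 33/0.85 = 38.8, so 39 per arm. This does not match.
- For scale, the stated inputs with 15% attrition: 63/0.85 = 74.1 and 64/0.85 = 75.3, so 75–76 per arm, or 150–152 in total.

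**4. Which outcome?** The largest SD a bounded score can have is half its range.

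- Raw NRS, 0 to 10 (section 2.6): at most 5.
- NRS change from a baseline of 3–6 (eligibility range, section 2.2.1): change lies between −6 and +7, so at most 13/2 = 6.5.

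An SD of 10 exceeds both limits, so the stated inputs cannot describe the radiating-pain NRS.

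**5. Baseline adjustment.** Section 2.7.2 plans a linear mixed model with baseline covariates. Let r be the baseline-to-week-7 correlation, with equal variances at the two times. The residual SD is then 10 × √(1 − r²) if 10 is a raw-score SD, and 10 × √((1 + r)/2) if it is a change-score SD. With 33 per arm and a 5-point difference:

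| r | Power, 10 = raw SD | Power, 10 = change SD |
|---|---|---|
| 0.02 | 52% | 80% |
| 0.5 | 64% | 64% |
| 0.7 | 80% | 58% |

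The two readings run in opposite directions and meet at r = 0.5, where √(1 − 0.25) = √(1.5/2) = 0.866. The article states neither r nor the kind of SD.

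**The case against.** The strongest reply is that 52% is the power of an unadjusted comparison, whereas the planned analysis adjusts for baseline. This stands as a limit on the claim. A reader might infer that the trial as analysed has only 52% power, or that adjustment would help only if the correlation were about 0.70. The document supports neither. The 0.70 threshold assumes that 10 is a raw-score SD, and under a change-score SD the pattern reverses. But section 2.3 makes no use of adjustment, so adjustment cannot explain how 33 was obtained.

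A second reply is that the sample size rests on previous research that is cited but not shown, so the printed inputs may be wrong rather than the number. That is possible, and only the sponsor can say which. It does not remove the inconsistency.

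Third, the consequence is partly contained: section 2.3 promises the two-sided 95% confidence interval for the primary difference, and an interval shows the imprecision of a null result. This softens the risk of misreading but does not correct the stated power.

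Two further inferences are tempting and go too far. One is that the calculation must be for the ODI. The figures rule out the NRS, but the text never names the ODI. The other is that a per-arm figure was mistaken for the total, since 63/0.85 = 74.1. That is a guess about origin. The lack of a separate calculation for the NRS is also not counted as a defect here, because a condensed article may leave it to the full protocol.

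**Conclusion.** The point holds, and section 2.3 is wrong as written. Its inputs need 63–64 evaluable per arm against 33 in Table 2, a shortfall of nearly half. By its own unadjusted method, the design has about 52% power for the stated 5-point difference (49% with 31 evaluable, 56% with all 37) and 80% power only for about 7 points at SD 10. The 15% and 10% attrition rates contradict each other, and only 10% is consistent with 37 per arm. The SD of 10 cannot belong to the radiating-pain NRS, and the outcome used is not named.

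The power figures assume a two-sample t-test, d = 0.5 and two-sided α of 0.05. The NRS limit of 6.5 for change assumes that baseline stays within the 3–6 eligibility range. The power of the adjusted analysis cannot be settled from the document; about 64% at a correlation of 0.5 is the one figure common to both readings of the SD.

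**What to change.** Correct section 2.3 and Table 2 so that the inputs and the sample size agree. No additional patients are needed for this.

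1. Name the primary outcome the calculation concerns, and the SD (raw or change score) and difference actually used.
2. If the printed inputs stand, remove the claim of 80% power for 5 points. State instead that 33 evaluable per arm gives 80% power for d = 0.70 (7 points at SD 10) and about 52% for 5 points in an unadjusted comparison. Because 5 points is described as the minimum clinically important difference, say openly that the detectable difference is larger than that. Amend the matching phrase in the Discussion.
3. Use one attrition rate in text and table. If it is 15%, show 31 evaluable per arm and about 49% power.
4. If power is meant to come from baseline adjustment, state the assumed correlation and which SD it applies to.

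The cost is a text and table correction and a less favourable stated power. Recruitment is under way (section 2.2), so it is best done before results are known.
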